#### Aim 2: Patient memory as a mediator of treatment condition and sleep and circadian functioning

Structural equation modeling (SEM) will be used to test whether patient memory for treatment contents at mid-treatment (i.e., session 4) and post-treatment mediates the relationship between treatment condition (TranS-C + MSI versus TranS-C alone) and the primary patient outcome of sleep disturbance and the secondary patient outcome of sleep-related impairment (measured by the PROMIS-SD and PROMIS-SRI respectively). Three simple mediation models will be specified for each of the two sleep and circadian dysfunction measures at each timepoint (post-treatment, 6FU, 12FU). For each model, the indirect effect of treatment condition to treatment outcome via patient memory will be assessed.

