#### Sleep and circadian functioning

Sleep and circadian functioning will be measured using a multi-method approach employing global, subjective (daily sleep diary), and objective (actigraphy) indices.

The *PROMIS Sleep Disturbance Scale* (PROMIS-SD) is an 8-item scale that will be used to assess perceived sleep problems (e.g., sleep quality, perception of sleep difficulties) over a 7-day period [85]. Items are rated on a 5-point scale ranging from 1 (not at all) to 5 (very much). Sleep disturbance will be measured at each assessment point (pre-treatment, post-treatment, 6FU, and 12FU). T-scores will be calculated from the sum of raw scores using treatment manuals for each timepoint. Higher scores indicate greater sleep disturbance. This scale has demonstrated moderate reliability and validity [85].

The *PROMIS Sleep Impairment Scale* (PROMIS-SRI) is an 8-item scale that will be used to assess perceived sleep problems during waking hours (e.g., alertness, sleepiness, tiredness) over a 7-day period [111]. Sleep impairment will be measured at each assessment point. Items are scored on a 5-point scale ranging from 1 (not at all) to 5 (very much). Higher scores indicate more sleep-related impairment. T-scores will be calculated from the sum of raw scores using treatment manuals for each time point.

The *Composite Sleep Health Score* (CSHS) will be used to calculate a cumulative score that indicates how well someone sleeps. CSHS will be measured at each assessment point. It is comprised of the sum of scores on 6 sleep health dimensions: regularity (midpoint fluctuation), satisfaction (sleep quality question on PROMIS-SD scale), alertness (daytime sleepiness question on PROMIS-SRI scale), timing (mean midpoint), efficiency (sleep efficiency), and duration (total sleep time) [112]. The satisfaction and alertness dimensions are drawn from questions on the PROMIS-SD and PROMIS-SRI scales respectively. All other dimensions are drawn from the daily sleep diary. Each dimension is dichotomized as either 0 = poor or 1 = good. For each dichotomized dimension, we will derive cut-off points for each dimension based on empirical literature and/or recommendations/consensus. Total sum scores range from 0 to 6, where higher scores indicate better sleep health.

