#### Memory assessments

Memory will be assessed using the Patient Treatment Recall Task and the Thoughts and Application Task at mid-treatment (between sessions 4 and 5), post-treatment, 6FU, and 12FU.

The *Patient Treatment Recall Task* will be used to assess participant memory for treatment contents [3]. Participants are required to spend a minimum of 5 min on the recall task and are given up to a maximum of 10 min to recall as many distinct treatment points as possible from all the sessions that they have attended so far (cumulative recall). This task has excellent interrater reliability and, in previous studies, is associated with the amount of memory support received [3, 121]. The overall number of treatment points recalled is determined using a scoring rubric developed in a previous study [3]. The number of treatment points will be summed at each measurement points to produce a single score.

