The potential contributions of this study should be considered alongside the protocol’s limitations. First, given that improving sleep can improve learning and memory consolidation [159], it is possible that TranS-C alone will boost patient memory for treatment. However, this is unlikely given that patient memory for treatment did not improve just with TranS-C—in the absence of memory support—in a previous study [160]. Nonetheless, to address this issue, patient memory for treatment will be evaluated in both treatment arms to rule out the possibility that TranS-C alone boosts memory for treatment. Second, patients will complete assessments by either phone or Zoom. To guard against the potential that the different cues available via these communication platforms might impact recall during the memory tasks, patients will be asked to turn off their cameras if using Zoom to better mimic the same conditions as those who take the assessment over the phone. In addition, daytime functioning and well-being were not included as inclusion criteria. Thus, it is possible that participants who have high baseline scores in these domains might mask any potential for improvement in these individuals.

These limitations notwithstanding, testing the efficacy of the MSI integrated into TranS-C has the potential to provide evidence for (a) the efficacy of a new simplified version of the MSI for improving patient memory for treatment with the goal of maintaining health, well-being, and functioning, (b) the wider application of the MSI for midlife and older adults and to the treatment of sleep and circadian problems, (c) the efficacy of treatment interventions delivered via telehealth to improve accessibility, and (d) the efficacy of the MSI for particular sub-groups who are likely to benefit from the intervention.

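### Aim 2 does not stop post-treatment recall from mediating sleep scores taken at the same assessment, and its covariate rule may leave out shared causes of memory and sleep

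*Protocol article*

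**What the plan says.** All references are to the protocol article.

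- **Mediator (Aim 2).** The plan tests whether "patient memory for treatment contents at mid-treatment (i.e., session 4) and post-treatment mediates the relationship between treatment condition" and sleep disturbance (PROMIS-SD) or sleep-related impairment (PROMIS-SRI).
- **Models (Aim 2).** "Three simple mediation models will be specified for each of the two sleep and circadian dysfunction measures at each timepoint (post-treatment, 6FU, 12FU"). In each, "the indirect effect of treatment condition to treatment outcome via patient memory will be assessed". No rule says which memory timepoint goes with which outcome timepoint.
- **Schedule.** Memory is tested "at mid-treatment (between sessions 4 and 5), post-treatment, 6FU, and 12FU" (Memory assessments). For the outcome, "Sleep disturbance will be measured at each assessment point (pre-treatment, post-treatment, 6FU, and 12FU") (Sleep and circadian functioning). Table 2 agrees and shows no PROMIS score at mid-treatment.
- **Look-back.** PROMIS-SD is used to "assess perceived sleep problems (e.g., sleep quality, perception of sleep difficulties) over a 7-day period"; PROMIS-SRI has the same 7-day window.
- **Priority.** The Participant measures section makes post-treatment the timepoint of main interest.
- **Reverse path (Discussion).** The authors allow that TranS-C alone might raise memory for treatment, "given that improving sleep can improve learning and memory consolidation". They consider this unlikely because it did not happen in an earlier TranS-C study, and they will measure memory in both arms.
- **Covariates.** Age, sex, presence of OSA and adherence to OSA treatment are named, the last three for sleep-related outcomes. Variables related to dropout are added. Others may enter if they are related to the outcome but unrelated to the predictor(s).

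**The concern.** A mediation claim needs the mediator to come before the outcome. In the pairing of post-treatment recall with post-treatment PROMIS it does not: the sleep score describes the week leading up to the visit at which recall is tested. The protocol itself names a route from sleep to memory, and a model of memory acting on sleep will absorb that route into its indirect effect.

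The second issue applies to every pairing. Randomisation protects the path from condition to memory but not the path from memory to sleep. The Background section links lower education, poorer baseline cognition and greater baseline severity to poor treatment response. The Objectives section expects these factors to modify effects on both memory and outcome. They are plausible shared causes, yet none is named as a covariate.

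At stake is the trial's main mechanistic conclusion, that memory support works through memory for treatment. It could be declared when memory plays no causal part.

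**Working it through.** **1. The plan's own Aim 2 figure.** The Sample size section gives 148 evaluable participants plus 20%: 148 × 1.20 = 177.6, rounded up to 178. This reproduces. The planning inputs are f = 0.18 (average constructive memory support to recall at *mid-treatment*) and f = 0.23 (*mid-treatment* recall to functional impairment at post-treatment). The detectable indirect effects at 6FU and 12FU are also stated via mid-treatment recall. Planning therefore used an ordered pairing and did not cover a post-treatment mediator.

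**2. Temporal order of the pairings that Aim 2 allows.**

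| Memory measured at | Outcome at | Mediator precedes outcome? |
|---|---|---|
| Mid-treatment | Post-treatment, 6FU, 12FU | Yes |
| Post-treatment | 6FU, 12FU | Yes |
| Post-treatment | Post-treatment | No: same assessment, 7-day look-back |

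**3. How large a false indirect effect can be.** Models: memory M on condition X (path a); sleep score Y on M and X (path b); indirect effect a × b. Monte Carlo settings: n = 148, 1:1 allocation, two-sided 0.05, joint-significance test, 4,000 trials per setting. The true effect of memory on sleep is zero throughout. Higher PROMIS is worse, so paths between sleep and memory are negative. The documents give no concurrent memory-sleep correlation, so these paths are assumptions shown as ranges. Condition-to-memory d = 0.36 (2 × 0.18) is also an assumption, because the planning f refers to a different predictor. The condition-to-sleep effect of d = 0.50 borrows the Aim 1 planning value.

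*(i) Sleep affects memory, and condition acts on sleep only (d = 0.50).* Paths 0, −0.2, −0.3, −0.4, −0.5: declared in 0.3%, 6%, 15%, 23%, 33% of trials.

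*(ii) As (i), plus a direct condition effect on memory of 0.36.* With unit within-arm variances, a = 0.36 + (−0.5 × path) and b = path. At path −0.3: a = 0.36 + 0.15 = 0.51, b = −0.3, a × b = −0.153 SD, where the truth is 0. Paths 0, −0.1, −0.2, −0.3, −0.4: declared in 3%, 16%, 53%, 84%, 92%.

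*(iii) Unmeasured shared cause, no condition effect on sleep.* b = −(residual correlation). At correlation 0.2: 0.36 × −0.2 = −0.072 SD.

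| Residual correlation | 0 | 0.1 | 0.2 | 0.3 | 0.4 |
|---|---|---|---|---|---|
| Declared, d = 0.36 | 3% | 14% | 41% | 56% | 59% |
| Declared, d = 0.50 | 5% | 19% | 59% | 83% | 85% |

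*(iv) Baseline sleep as the shared cause.* Baseline-to-post correlation 0.5, baseline-to-memory path −0.2 to −0.4, condition-to-memory d = 0.36 or 0.50. At path −0.3 and d = 0.36: b = 0.5 × −0.3 = −0.15, and a × b = 0.36 × −0.15 = −0.054 SD. Across the range, declared in 13% to 57% without the baseline outcome and 2% to 5% with it.

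**4. What each part of a repair does (d = 0.36).**

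- Same-visit mediator *with* the baseline outcome: still 85% to 94% at sleep-to-memory paths of −0.3 to −0.4. The exact rate moves with the other assumed paths.
- Mid-treatment mediator *without* the baseline outcome (baseline-to-memory path −0.3): about 26%.
- Mid-treatment mediator *with* the baseline outcome: about 3%, if sleep has not changed before session 4 and there is no other shared cause.

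Baseline adjustment therefore does not rescue the same-visit pairing, and correct ordering alone does not remove shared causes.

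**The case against.** The other side has several fair points.

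- **The pairing is not spelled out.** Aim 2 never says that post-treatment memory will be matched to post-treatment PROMIS, and the Sample size section uses mid-treatment recall. This stands in part: the text may only need its pairings stated. As written, however, it names a post-treatment mediator and post-treatment outcomes without separating them.
- **The Discussion answers the reverse path.** Its answer concerns whether TranS-C alone raises memory. That is fair context, but it does not settle which way the recall-sleep association runs inside the model.
- **Exclusion of the baseline outcome is not stated.** A reader might infer it from the word simple and from the covariate list. The documents do not support that: simple can mean a single mediator, the list is not closed, and a fuller analysis plan could add the baseline score. If predictor means treatment condition only, baseline PROMIS would pass the covariate rule. If memory counts as a predictor in the outcome equation, the rule screens out exactly the variables related to both. The text leaves this open.
- **A single false-positive rate would mislead.** A reader might treat the planning value f = 0.23 as wholly spurious and quote 44% to 57%. That is ordinary power at N = 142 to 178 under another name, with inputs from a different predictor and outcome.
- **The number of tests is uncertain.** The sentence on three models can be read as 3 × 2 × 3 = 18, or as one model per measure and timepoint, 2 × 3 = 6. No multiplicity claim should rest on it.
- **Confounding of an unrandomised mediator is common to all mediation analyses.** True, and the repair reduces it without removing it.

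**Conclusion.** The concern holds for one pairing and, more weakly, for the covariate rule. Post-treatment recall with post-treatment PROMIS has no temporal order, and it falls at the timepoint of main interest. A significant indirect effect there supports an association, not mediation. It would be wrong to conclude that all of Aim 2 is mis-ordered: mid-treatment memory with any outcome, and post-treatment memory with 6FU or 12FU, are in the right order though still open to shared causes.

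The size depends on paths that the documents do not give. With no effect of memory on sleep, false declarations range from about 0.3% to over 90%. Rates are low when memory and sleep are otherwise unrelated, and high when sleep affects recall and condition affects both. The same-visit conclusion does not depend on whether baseline PROMIS is adjusted for. The wording should be changed before analysis; the randomised Aim 1 comparison is unaffected.

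**What to change.** In the Aim 2 section:

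1. Name mid-treatment recall as the mediator for post-treatment outcomes, as the Sample size section already assumes, and use post-treatment recall only for 6FU and 12FU outcomes.
2. Adjust both the mediator and the outcome equation for the pre-treatment value of the outcome, age, education, baseline MoCA/CFQ, sex and OSA status. State that the rule in the Covariates section does not exclude mediator-outcome confounders in Aim 2.
3. Report any same-visit model as an association only.
4. Keep post-treatment PROMIS out of the main models. In the mediator equation it would condition on a variable affected by treatment. In the outcome equation it would remove any memory effect that passes through post-treatment sleep. At most, use it in the outcome equation of the follow-up models as a sensitivity analysis.

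**Cost.** This is a change of wording, and every variable is already collected. The same-visit pairing loses its causal label. Sleep change before session 4 still cannot be adjusted for, because PROMIS is not measured at mid-treatment; the report should say so.

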#### Aim 3: Poor treatment response sub-groups as a moderator of treatment condition and sleep and circadian functioning

HLMs will be used to assess the relationship between treatment condition and outcomes at post-treatment, with the following sub-groups included as moderators: age, education, cognitive functioning,^1^ and severity of sleep disruption and sleep-related impairment. These moderators are included in the analysis to assess whether constructive memory support received in the TranS-C + MSI treatment condition results in greater treatment outcomes in any of the sub-groups.

### Interim analyses {21b}

There are no interim analyses planned.

### Methods for additional analyses (e.g., subgroup analyses) {20b}

#### Exploratory Aim 1: Treatment effects on patient adherence, patient-rated treatment credibility, and utilization of treatment elements

An independent samples *t*-test will be used to determine if patient ratings of credibility at the start of treatment differ between TranS-C + MSI compared to TranS-C alone. An independent samples *t*-test will also be used to determine whether average patient adherence during treatment differs between treatment condition. HLMs will be used to determine if participant ratings of their utilization of treatment elements differ by treatment condition from pre- to post-treatment, 6FU, and 12FU.

#### Exploratory Aim 2: Treatment effects on therapist-rated acceptability, appropriateness, and feasibility

Independent samples *t*-tests will be used to determine if therapist ratings of acceptability, appropriateness, and feasibility measured in Session 8 differ between the two treatment conditions (TranS-C + MSI versus TranS-C alone).

#### Exploratory Aim 3: Effects of constructive memory support type on outcomes

HLMs will be used to determine which constructive memory support strategies are associated with the greatest improvement in outcomes at post-treatment, 6FU, and 12FU.

### Fidelity checks

To assess therapist competence and fidelity to treatment, data from the Provider-Rated TranS-C Checklist, checklist of treatment elements specific to TranS-C, and the Memory Support Treatment Provider Checklist will be reported. The Memory Support Treatment Provider Checklist will be used to evaluate whether providers delivered the recommended dose of memory support.

### Manipulation check

To check the assumption that the MSI will effectively result in the delivery of constructive memory support and manipulate patient recall during the TranS-C, independent samples *t*-tests will be used to assess if the total amount of constructive memory support, the different number of types of constructive memory support (measured by the MSRS), and patient recall will be greater in the TranS-C + MSI condition compared to TranS-C alone.

### Methods in analysis to handle protocol non-adherence and any statistical methods to handle missing data {20c}

All analyses will be based on the intent-to-treat principles [149]. Participants who are randomized to treatment condition will be included in the final analyses. We will continue to collect follow-up assessments from participants who withdraw from treatment or are non-adherent to treatment. The *N* by stage of dropout will be reported for the following: dropout after randomization but before the first treatment session, dropout after treatment has begun but before treatment has been completed, and dropout after treatment has been completed but prior to post-treatment, 6- or 12-month follow-up assessments. The number of participants who completed a post-treatment assessment but were lost to 6- and/or 12-month follow-up will also be reported. When available, the reasons for dropout and improvement among participants who dropout will be reported.

For analyses that will use HLM and SEM will use all available data (intent-to-treat). Models will be estimated with maximum likelihood estimation, and missing data will be assumed to be missing at random [149] and has been shown to perform well in simulations of HLM’s with missing data up to 50% [150]. For all other analyses, approaches for handling missing data will be based on the number of missing cases (e.g., listwise deletion vs. multiple imputation).

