### Covariates

If dropout is associated with other variables, these variables will be added as predictors to reduce bias. Baseline differences between groups will be examined (e.g., demographics); however, these tests will not be used to select covariates in the primary intent-to-treat analysis. Instead, the potential influences of baseline differences will be evaluated as moderators. The stratification factor (age) will be included as a covariate, per recommendations [151]. Additional covariates may be included if they are associated with the outcome but not the predictor/s. Sex will be included as a covariate in sleep-related outcomes, given the substantial body of literature identifying sex-related differences in sleep problems [80, 152–154]. Presence of OSA and adherence to OSA treatment are likely to influence sleep-related outcomes and will be included as covariates in analyses with these outcomes. Presence of OSA will be dummy-coded as mild and moderate/severe with no diagnosis as the reference group. Adherence to OSA treatment will be dummy-coded as yes with no as the reference group.

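### Aim 2 mediation at 6FU and 12FU: single-wave models ignore earlier PROMIS scores for people lost to follow-up, and adding dropout correlates as predictors could remove much of the indirect effect

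*Protocol article*

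**What the plan says.** All references are to the protocol article.

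- **Model structure** (Aim 2 under Statistical methods): "Three simple mediation models will be specified for each of the two sleep and circadian dysfunction measures at each timepoint (post-treatment, 6FU, 12FU". Whether this means three models per measure or three per measure and timepoint, each model has one outcome wave. The target is the indirect effect: "For each model, the indirect effect of treatment condition to treatment outcome via patient memory will be assessed". No earlier PROMIS wave is named in the 6FU or 12FU models.
- **Missing data** (section {20c}): HLM and SEM share one statement, "For analyses that will use HLM and SEM will use all available data (intent-to-treat", followed by "Models will be estimated with maximum likelihood estimation, and missing data will be assumed to be missing at random".
- **Covariates**: "The stratification factor (age) will be included as a covariate, per recommendations"; "Sex will be included as a covariate in sleep-related outcomes"; "Presence of OSA and adherence to OSA treatment are likely to influence sleep-related outcomes and will be included as covariates". For dropout: "If dropout is associated with other variables, these variables will be added as predictors to reduce bias". Nothing restricts that last rule to variables measured before randomisation.
- **Standing of the waves** (Sample size {14}): post-treatment is the powered timepoint. At 6FU and 12FU effect sizes are to be emphasised over significance.

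**The concern.** One missing-data sentence covers two kinds of model that do not have the same protection. In the Aim 1 HLM, a participant lost at 12FU still contributes pre-treatment, post-treatment and 6FU scores, and missing at random is conditional on them. In a 12FU mediation model, the same participant informs the arm-to-memory path but not the memory-to-outcome path. Missing at random is then conditional only on arm, memory and whatever covariates are in that model.

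If people with poor post-treatment PROMIS are more likely to leave, the protocol's text offers two routes. Leaving post-treatment PROMIS out means missing at random fails for that model. Adding it as a predictor changes the quantity estimated: post-treatment PROMIS is measured after mid-treatment recall, so it can lie on the route from memory to later PROMIS, and conditioning on it removes the part of the effect that runs through early improvement. Because follow-up results will be read as effect sizes, bias in the estimate matters directly.

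**Working it through.** **Inputs from the protocol.** Aim 2 sample size: 148 × 1.2 = 177.6, rounded up to 178, which matches the stated figure. Arm-to-memory f = 0.18; for two equal groups d = 2f = 0.36. Memory-to-outcome f = 0.23, used as a standardised path of −0.23 (higher PROMIS is worse). The protocol's f values come from another trial and from functional impairment at post-treatment, so using them for 12FU PROMIS is an assumption.

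**Assumptions not in the protocol.** Dropout mechanism and rate, correlations between waves, and the share k of the memory effect on 12FU PROMIS that passes through post-treatment PROMIS.

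**Step 1: who informs the path.** With 20% missing at a wave, 178 × 0.8 ≈ 142 participants inform the memory-to-outcome path. The other 36 or so inform only arm-to-memory.

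**Step 2: post-treatment PROMIS left out.** Let M be memory, Y0 pre-treatment, Y1 post-treatment and Y3 12FU PROMIS:

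- Y1 = 0.5·Y0 − 0.23·M + error
- Y3 = k·Y1 + 0.2·Y0 − 0.23·(1−k)·M + error, with k = 0.5 or 0.7

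The total effect of M on Y3 is k·(−0.23) − 0.23·(1−k) = −0.23. With 20–30% missing and log-odds of dropout rising 0.5–1.5 per SD of Y1, the single-wave path is about 2–18% too close to zero. Adding only pre-treatment PROMIS as a covariate still leaves about 1–12%. Earlier waves used as auxiliary variables bring it within about 1% of the full-data value. Example (20% missing, log-odds 1.0, k = 0.7): full data −0.229, single-wave −0.210, auxiliary −0.230.

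**Step 3: other dropout mechanisms.** A second simulation used d = 0.36, path −0.23, direct effect −0.2 and a residual correlation of 0.6 between waves. The table gives the single-wave indirect effect as a ratio to its full-data value.

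| Dropout depends on | 20% missing | 35% missing |
|---|---|---|
| nothing (completely random) | 1.00 | 1.00 |
| arm and memory | 1.00 | 1.02 |
| high post-treatment PROMIS | 0.91 | 0.89 |
| high PROMIS and low memory | 0.70 | 0.56 |
| high PROMIS and high memory | 1.21 | 1.28 |
| PROMIS × memory, positive | 1.37 | 1.57 |
| PROMIS × memory, negative | 0.47 | 0.23 |

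With post-treatment PROMIS as an auxiliary variable the ratio is 0.99–1.01 in every row.

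**Step 4: post-treatment PROMIS as a predictor.** In the Step 2 model, conditioning on Y1 and Y0 leaves only −0.23·(1−k): −0.115 for k = 0.5 and −0.069 for k = 0.7, cuts of 50% and 70%. Conditioning on Y1 but not Y0 leaves −0.23·(1 − k − 0.2c), where c is the slope of Y0 on Y1 given M. With c = 0.5 (unit variances) the cuts are 60% and 80%. The simulations give about 60–81%; in the Step 2 example the path becomes −0.043, and 1 − 0.043/0.229 = 81%.

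**Step 5: precision.** With completely random 20% loss and 178 participants, the SD of the path is 0.0833 single-wave, 0.0805 with the auxiliary variable and 0.0743 with complete data. The variance ratio is (0.0833/0.0805)² ≈ 1.07. The Step 2 model gave 8–21% excess variance.

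**The case against.** **The covariate rule already covers this.** The models are not limited to arm, memory and one outcome: age, sex, OSA and OSA-treatment adherence enter, and earlier PROMIS would qualify under the dropout rule if it predicts dropout. That is correct, and a reader should not infer otherwise. But the rule brings it in as a predictor, which is the more damaging route in Step 4.

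**A reader might infer a contradiction with the all-available-data statement.** There is none. Maximum likelihood uses every observed value of the variables in the model, and people missing 12FU still inform the arm-to-memory path. The protocol does not promise that every wave enters every model.

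**A reader might infer that the indirect effect is always pulled towards zero.** Step 3 shows otherwise, and the documents do not say which dropout mechanism will operate.

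**The omission bias is small.** In the Step 2 example it is 0.019 against an SD of 0.083, under a quarter of an SD. This holds for dropout on post-treatment PROMIS alone; Step 3 includes larger distortions.

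**The 60–81% is built in.** Largely so: it follows from the assumed k. The mechanism does not depend on k, but the size does. The rule also never names post-treatment PROMIS. And where post-treatment rather than mid-treatment recall is the mediator, the two are measured at the same assessment, so their order is not established.

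**Auxiliary variables are analysis-plan detail.** As an omission, that would be fair. Here the article itself fixes single-wave models and a predictor rule without a time limit, and those stated choices are the issue.

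**Conclusion.** The point holds for the 6FU and 12FU mediation models and is conditional on how dropout arises. If it depends on post-treatment PROMIS, the plan as written either omits that score (path about 2–18% too small when dropout depends on it alone; ratios of 0.23 to 1.57 under the other mechanisms tried) or conditions on an intermediate outcome (path cut by about 60–81% under the assumed k). If dropout is random or depends only on arm and memory, omission causes no bias.

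The unrestricted predictor rule is the more serious part; the single-wave structure alone is milder. The case rests on bias, since the precision gain is modest and depends on assumptions. The checks concern a follow-up wave only and do not show that the powered post-treatment mediation is affected; the only earlier PROMIS scores there predate randomisation. A correction should be made, but it does not touch the primary timepoint.

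**What to change.** In Covariates, restrict the dropout rule for the Aim 2 SEMs: only variables measured before randomisation may be added as predictors. In Aim 2 and section {20c}, state that the other PROMIS-SD and PROMIS-SRI waves, and any other post-randomisation correlates of dropout, enter as auxiliary variables, that is, allowed to correlate with the model residuals without predicting the outcome. Alternatively, fit one SEM per measure with all four PROMIS waves, provided the reported indirect effect is the total effect through memory, including the part that passes through earlier PROMIS.

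The cost is a sentence or two of analysis wording and slightly larger models. No new data or participants are needed.
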